### Data collection

Clinical data will be collected on the following baseline staging investigations and treatment details (box 1).Box 1Baseline staging investigations and treatment details**Baseline characteristics**Patient demographicsCharlson comorbidity scoreBlood tests (full blood count, serum urea and electrolytes, liver function tests, carcinoembryonic antigen)**Clinical presentation****Cancer stage at presentation**Location and stage (TNM/Dukes) of colorectal primaryLocation, number and size of liver metastasesfluorodeoxyglucose positron emission tomographyRectal MR (if applicable)**Preoperative workup**Portal vein embolisationCardiopulmonary exercise test**Surgery (staged/synchronous resections)**Sequence of surgeryOpen/laparoscopicOperative timeEstimated blood loss/transfusionBowel resectionPrimary anastomosisCovering stoma**Liver resection**Major resection (>3 Couinaud segments)Pringle timeComplications (Clavien-Dindo)Critical care stayTotal inpatient stayReadmission within 30 days30-day mortality**Chemotherapy (neoadjuvant/adjuvant)**RegimeNumber of cycles (planned/given)Duration of treatmentSide effects (common terminology criteria for adverse events)Restaging**Outcomes (1, 2 and 5 years)**Disease-free survivalDisease progression**Quality of life**EuroQol with 5 dimensions with 3 levels of severity (EQ-5D-3L)European Organization for Research and Treatment of Cancer Core Quality of Life Questionnaire (EORTC QLQ-C30)European Organization for Research and Treatment of Cancer Colorectal Cancer Liver Metastasis specific module (EORTC QLQ LMC)

In addition to demographic detail, baseline staging will include tests for histological confirmation of cancer such as biopsy confirmation of a diagnosis of primary colorectal cancer (from the primary and not from the metastasis); tests for assessment of the liver and colorectal cancer in terms of lesion size, number, nodal involvement: contrast-enhanced CT scan and/or contrast-enhanced MR scan of the liver and pelvis and tests for assessment of the presence or absence of extrahepatic metastatic disease such as [^18^F]FDG-PET scan and serum assay of carcinoembryonic antigen. All of these tests are components of standard clinical care and no additional tests are undertaken for research purposes.

#### Predictors of treatment allocation

Factors which guide clinical decision making in terms of the use of neoadjuvant chemotherapy and the choice of intervention (synchronous or sequential surgery).

#### Timelines for completion of the treatment protocol

For the purposes of this study, this is defined as the amount of time in days from enrolment to completion of the protocol. The term ‘protocol’ relates to completion of the common treatment pathway.

#### Failure to complete the treatment protocol

This is defined as dropout prior to completion of the allocated treatment sequence. It will be further categorised as due to disease progression, patient choice or unrelated to colorectal cancer (for example myocardial infarction) and will be recorded as the time in days from enrolment.

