The second category of patients with liver-limited synchronous metastases represents a common and increasingly complex clinical management problem.^13^ Traditional management (referred to variously as the classical or staged approach) comprised resection of the colorectal primary tumour followed by adjuvant chemotherapy with liver resection being undertaken (if at all) as a subsequent operation.^13–15^ Key advances in the availability and safety of liver surgery, anaesthesia and critical care have made two alternative options feasible for patients with synchronous disease. The first is synchronous resection of the liver metastases and the colorectal primary.^13 15^ This has the attraction of removing the macroscopic tumour burden with a single operation. However, the morbidity of complex liver resection combined with major bowel resection may be considerable and there is some evidence of a negative effect on progression-free survival.^16^ The second option is resection of the liver metastatic disease as the first step, termed the reverse or liver-first approach.^17 18^ Liver-first surgery may be particularly applicable to patients with rectal cancer with synchronous liver metastases where preoperative long-course chemoradiotherapy for the rectal primary prior to surgical resection creates a potential ‘window’ in which liver resection may be undertaken.^19 20^ The liver-first strategy may also be oncologically advantageous by addressing the hepatic metastatic burden before progression in the liver renders this unresectable.^21^ A further potentially important benefit of the liver-first approach is that pelvic surgery may be either avoided or less extensive in patients with rectal tumours with a complete endoscopic, radiological and clinical response to chemoradiotherapy.^22^

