#### Complication and treatment-related morbidity profiles

Complications will be recorded prospectively according to the criteria defined above (see treatments) and assessed at the end of the study. Operative outcomes will be reported in keeping with the Dindo-Clavien system of assessment of postoperative morbidity.^29^ The specific posthepatectomy complications of haemorrhage,^30^ bile leakage^31^ and liver failure^32^ will be recorded in compliance with the guidance of the International Study Group of Liver Surgery. The morbidity associated with each intervention step will be recorded separately. Morbidity will include unplanned readmission and reoperation. Requirement for non-elective surgery for colonic complications (obstruction, perforation, bleeding) will be recorded.

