#### Mortality

Overall and cancer-related mortality in either arm after enrolment will be recorded. Mortality (and cause) will be determined using the Demographics Batch Service to access the national electronic database of the UK NHS.

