### Study size

Based on clinical registers, the HPB unit at Manchester Royal Infirmary sees approximately 75 patients with colorectal cancer with synchronous liver-limited hepatic metastases per annum. As there are no study-related interventions, recruitment rates should be high and dropout low and is estimated to provide 150 patients in the 2-year recruitment period. A formal power calculation is not provided for this inception cohort study. Instead, the sample size is informed by the need to: provide stable estimates of variance for a range of outcomes; explore the relationship between the treatment pathway and health outcomes; estimate acceptability and recruitment rates; and describe patient and clinician experiences.

Purposeful sampling will be used to select patients from the cohort for the qualitative study. It is estimated that a sample size of four to six patients per group and one to two clinicians will produce data saturation. However, we will continue to interview until data saturation is reached.

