### Analysis plan

The care of patients within the study pathway will be characterised by their principal treatment route as synchronous, liver first or bowel first. All patients will provide outcomes which will be included within analyses, grouped according to the treatment sequence received. Complication profiles in patients according to treatment group will be reported.

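### The causes listed for failing to complete treatment include no treatment-related and no other category, so failures from complications, toxicity or treatment-related death have no proper code

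*Protocol article*

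**What the plan says.** Under Failure to complete the treatment protocol, the article defines the outcome: "This is defined as dropout prior to completion of the allocated treatment sequence". It is timed in days from enrolment, and its causes are set out in one sentence: "It will be further categorised as due to disease progression, patient choice or unrelated to colorectal cancer (for example myocardial infarction"). In that sentence, the words introducing an example attach only to the infarction. The list of three causes is not presented as illustrative.

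The Analysis plan has patients "characterised by their principal treatment route as synchronous, liver first or bowel first", with outcomes grouped by the sequence received. The second of the primary aims is comparable outcome data for synchronous and sequential surgery.

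The Background gives two reasons why non-completion might depend on sequence. For synchronous resection, "the morbidity of complex liver resection combined with major bowel resection may be considerable". For liver-first surgery, a possible advantage is "addressing the hepatic metastatic burden before progression in the liver renders this unresectable".

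Treatment harm is captured in other places. Under Complication and treatment-related morbidity profiles, "The morbidity associated with each intervention step will be recorded separately". Box 1 lists Clavien-Dindo complications, 30-day mortality, chemotherapy side effects on the common terminology criteria, and cycles planned and given. Under Mortality, "Overall and cancer-related mortality in either arm after enrolment will be recorded", and cause of death is obtained. Adverse event reporting adds an assessment of severity and attribution.

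**The concern.** A patient can stop because of liver failure after hepatectomy, a complication of bowel surgery or toxicity from chemotherapy, or can die around an operation, without having progressed and without having chosen to stop. The only remaining label is defined by its relation to the cancer and says nothing about its relation to treatment. Its single example, myocardial infarction, can equally be a background event or a consequence of surgery, and no rule separates the two.

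What is at stake is the interpretation of one outcome in the comparison of sequences. Whether a route prevents its own completion is a natural question to ask of synchronous and staged surgery. In the staged routes, a complication of the first operation can prevent the second. As defined, the cause-of-failure outcome can mix that harm with unrelated loss.

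**Working it through.** **Step 1. The plan's own figure.** The only size figure is the expected cohort. Study size states that the unit "sees approximately 75 patients with colorectal cancer with synchronous liver-limited hepatic metastases per annum", over a 2-year recruitment period: 75 × 2 = 150, which agrees with the stated 150. No power calculation is given, and adding a category changes no figure in the article.

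**Step 2. Cases set against the three codes.**

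| Reason for stopping | Progression? | Patient choice? | Unrelated to the cancer? |
|---|---|---|---|
| Liver failure after hepatectomy, bowel stage not reached | No | No | Not caused by the tumour, but caused by treating it |
| Chemotherapy toxicity, remaining cycles not given | No | Only if the patient declines | As above |
| Myocardial infarction during recovery from resection | No | No | Matches the worked example, although it may be due to surgery |
| Perioperative death | No | No | Unclear; the text does not say whether death counts as dropout |
| Myocardial infarction remote from any treatment | No | No | Yes |

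Only the last row has a clean home. The third row shares that code with it, so the code cannot separate them.

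**Step 3. Can the other records replace the missing code?** Box 1 and the sections on complications, mortality and adverse events record the events themselves. None of them records that an event was the reason for stopping. A patient may have a complication and stop for another reason, so deriving the cause afterwards means inferring it.

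**Step 4. Illustration of size.** No failure rates are in the documents, so all the rates here are assumptions. Let u be the proportion with truly unrelated failure and t the proportion with treatment-related failure, and suppose every treatment-related failure is filed as unrelated. The treatment-related share of that category is t / (t + u).

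With u = 5%:

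- t = 2%: 2/7 = 29%
- t = 5%: 5/10 = 50%
- t = 10%: 10/15 = 67%
- t = 15%: 15/20 = 75%
- t = 20%: 20/25 = 80%

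The share depends on u. At u = 2% the range over the same t is 2/4 = 50% to 20/22 = 91%. At u = 10% it is 2/12 = 17% to 20/30 = 67%.

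In counts, assume equal groups of 150/3 = 50. Then u = 5% is 2.5 expected patients, and t from 2% to 20% is 1 to 10. If one group had t = 5% and another t = 15%, the unrelated category would hold 10% and 20%, or 5 and 10 patients. The whole 10-point difference would be treatment harm under a label that says otherwise.

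**The case against.** The strongest reply has four parts.

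- **The list may not be closed.** The article does not call the three causes exhaustive, and it condenses a fuller protocol in which a residual code might appear. This stands in part. A reader might infer that treatment-related failures will be coded as unrelated or as patient choice, but the documents do not say so. Such cases could also be left uncoded or placed under progression. What remains is that the published definition lists three causes without qualification and gives no rule for these cases.
- **The third label can be read literally.** It refers to the cancer, so a postoperative infarction or drug toxicity may fall under it without being false. On that reading the category is coarse, not wrong. Coarseness is still the problem here, because it pools treatment harm with background events.
- **The information exists elsewhere.** Step-level morbidity, toxicity, deaths and adverse-event attribution are all collected, and complication profiles are to be reported by treatment group. This stands. A reader might conclude that treatment-caused failure would be reported as nil, or that the routes could not be compared on treatment harm. Neither follows. The limitation belongs to this one outcome, not to the study's morbidity reporting.
- **Progression depends on sequence too.** The Background says so, and the section acknowledging selection bias names progression after bowel-first surgery as a source of loss. This also stands. A reader might take treatment-related failures to be the ones most likely to differ between sequences, but the documents do not rank the mechanisms. They support only that such failures may differ.

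The study is also exploratory, with no power calculation, and counts per category will be small. That limits what the outcome can show but does not justify an ambiguous label.

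**Conclusion.** The point holds in a limited form. The definition has no place for treatment-related failures and no residual category, and its one example blurs perioperative and background events. Followed as written, the outcome cannot by itself tell whether a sequence stops patients completing care through its own morbidity.

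The size is unknown. The 29% to 80% contamination of the unrelated category rests on an assumed 5% unrelated failure rate, assumed treatment-related rates of 2% to 20%, and the worst case that all such failures are filed there. It shows what could happen and does not estimate what will. No stated study figure is affected and the design is not undermined. The definition should be corrected because a named outcome in the sequence comparison is otherwise hard to interpret.

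**What to change.** Amend the definition of failure to complete as follows:

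- Add a treatment-related category covering surgical complication, chemotherapy toxicity and treatment-related death, and add an other category.
- Restrict unrelated to events attributed to neither the cancer nor its treatment.
- State whether death before completion counts as failure, and how deaths and perioperative medical events are classified.
- Assign the cause from the Clavien-Dindo, common terminology criteria, cause-of-death and adverse-event attribution data already collected, and record the treatment step to which it relates.
- Report cause of failure by sequence group.

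The cost is one or two extra codes on the case report form and a derivation from existing data. With about 150 patients in three groups, counts per category will be small, so descriptive reporting is enough.

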#### Disease-free survival 12 months after enrolment into protocol

This is defined as the absence of tumour on a CT scan of the thorax, abdomen and pelvis undertaken at the completion of the protocol. In the case of those patients with rectal tumours treated by a’ watch and wait ‘policy, the term disease free can only be applied if there is a combination of radiological, endoscopic and clinical evidence of absence of cancer.

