**Methods and analysis:**

Colorectal cancer with Synchronous liver-limited Metastases: an Inception Cohort (CoSMIC) is an inception cohort study of patients with a new diagnosis of colorectal cancer with synchronous liver-limited metastases. The sequence of treatment received, and factors influencing treatment decisions, will be evaluated against European Society of Medical Oncology guidelines. Clinical data will be collected, and quality of life, morbidity, mortality and long-term outcome compared for different treatment sequences adjusted for prognostic factors. Disease-free survival or progression will be measured at 1, 2 and 5 years. A nested qualitative study will ascertain patient experiences and clinician perspectives on delivery of care.

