#### Disease progression in patients who are not disease free at the end of protocol

The most sensitive measure of change is likely to involve a metric incorporating tumour size and number of lesions in the case of multiple metastases. There is evidence that CT-based volumetric assessment of metastases (seeded region growing method, slice-based segmentation or threshold-based segmentation) is more accurate for assessment of disease progression than the Response Evaluation Criteria In Solid Tumors (RECIST) V.1.1 method of largest axial diameter.^24^ It is acknowledged that although RECIST criteria provide an objective means of assessment of solid tumour response to treatment, there is a risk of interobserver bias.^25^ Further, RECIST criteria may be insufficient to assess response to treatment in patients with colorectal liver metastases treated by biological agents such as bevacizumab.^26^ Thus, disease progression at end of protocol will be assessed both by RECIST V.1.1 criteria and volumetric assessment.

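### Disease-free survival is labelled as a 12-month outcome but read from a CT at the end of treatment, so the time varies by patient and those who die or drop out first have no value

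*Protocol article*

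**What the plan says.** The relevant statements are all in the protocol article.

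- The outcome is headed "Disease-free survival 12 months after enrolment into protocol". The text beneath defines it as "the absence of tumour on a CT scan of the thorax, abdomen and pelvis undertaken at the completion of the protocol". For rectal tumours managed by watch and wait, it requires radiological, endoscopic and clinical evidence together.
- Timelines for completion of the treatment protocol measures "the amount of time in days from enrolment to completion of the protocol" and explains that the word protocol "relates to completion of the common treatment pathway".
- The abstract says "Disease-free survival or progression will be measured at 1, 2 and 5 years". Box 1 and the Dissemination policy give the same three time points.
- The progression section says that "disease progression at end of protocol will be assessed both by RECIST V.1.1 criteria and volumetric assessment".
- Failure to complete the treatment protocol is a separate outcome: "This is defined as dropout prior to completion of the allocated treatment sequence". It is classified by reason, with disease progression among the reasons, and timed in days from enrolment.
- The Mortality section records overall and cancer-related deaths but does not link them to disease-free status.
- The Analysis plan says that all patients contribute outcomes, grouped by the sequence they actually had.

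**The concern.** The heading and the definition name two different moments. Completion of the pathway coincides with 12 months after enrolment only by chance, and the article treats time to completion as something to be measured. An analyst following the definition would report tumour status at the end of treatment under a 12-month survival label.

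The definition also needs a scan that some patients cannot have. Those who die, or who leave the pathway because of progression, choice or unrelated illness, do not reach the completion CT. Many of them are the patients in whom treatment failed, so their missing values carry information about the outcome. An endpoint with survival in its name also has no rule for death.

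This matters because one of the study's primary aims is comparable outcome data for synchronous and sequential surgery. Adjustment for prognostic factors does not repair an outcome read at varying times and absent for a selected group of patients.

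**Working it through.** **1. The plan's own figure.** Study size gives about 75 eligible patients a year over a 2-year recruitment period: 75 × 2 = 150, as stated. There is no power calculation, so nothing in the sample size depends on this endpoint. The 150 serves below only as the denominator.

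**2. Time of reading.**

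| Place in the protocol article | Time implied |
|---|---|
| Heading of the outcome | 12 months from enrolment |
| Definition under that heading | Completion of the protocol |
| Timelines section | Completion means the treatment pathway; days to completion vary |
| Progression section | End of protocol |
| Abstract, Box 1, Dissemination policy | 1, 2 and 5 years |

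The second, third and fourth rows agree with each other, and so do the first and fifth. The two sets do not agree. A single CT at completion also cannot supply the 2-year and 5-year readings.

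**3. Who has a value.**

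- Completed pathway, CT clear: disease-free.
- Completed pathway, CT not clear: not disease-free; passes to the progression measure.
- Left the pathway early for progression, choice or unrelated illness: no completion CT, no value.
- Died before completion: no completion CT, no value.

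The last two groups are captured under Failure to complete and Mortality, but no rule places them as disease-free or not. That is incompatible with all patients contributing outcomes, at least for this endpoint.

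**4. How much the missing rule can matter.** The article gives neither a disease-free rate nor a non-completion rate, so both are assumed. Let r be the proportion disease-free among completers and d the proportion not completing.

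- Left out: r
- Counted as not disease-free: r(1 − d)
- Counted as disease-free (an upper bound only): r(1 − d) + d

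With r = 60%:

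| d | Patients of 150 | Left out | As failures | As disease-free |
|---|---|---|---|---|
| 10% | 15 | 60% | 0.60 × 0.90 = 54% | 54% + 10% = 64% |
| 20% | 30 | 60% | 0.60 × 0.80 = 48% | 48% + 20% = 68% |
| 30% | 45 | 60% | 0.60 × 0.70 = 42% | 42% + 30% = 72% |

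The gap between leaving patients out and counting them as failures is r × d. For r from 50% to 70% it is 5 to 7 points at d = 10% and 10 to 14 points at d = 20%. The article does not say which treatment applies.

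**5. Reading time by sequence.** The article gives no completion times, overall or by sequence. Two features make a difference plausible. One route has a single operation and the others two. The Recruitment section also admits patients whose treatment has already begun, typically after an acute bowel presentation, which shortens their interval from enrolment to completion. Neither feature gives a number.

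**The case against.** The other side has four fair points.

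First, a reader might infer that sequences finishing early are scanned early, have had less time to recur and so look better, and might put a size on this with a constant relapse hazard from enrolment. The documents do not support that. The inclusion criteria require hepatic metastases, so no one is disease-free at diagnosis and tumour is cleared during the pathway. A patient completing late may have been cleared as recently before the scan as one completing early. Without completion times, even the direction of any bias is unknown. This objection stands.

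Second, a reader might infer that the plan scores only completers. It states no such analysis. It says all patients contribute, and it records the reason for and timing of non-completion as well as deaths. This stands too: the data to classify these patients will exist, and what is lacking is a definition that uses them.

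Third, such rules are often left to an analysis plan or full protocol. That would answer a missing detail. Here the article states the definition itself, and it contradicts its own heading. The general remark in Recruitment about imputing missing data points does not help. Its stated focus is quality of life before surgery, and imputing a scan result for someone who has died would not be meaningful.

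Fourth, no primary endpoint is named, analyses are exploratory and reporting is meant to be descriptive. This limits the consequences. A descriptive percentage still needs one time point and one denominator.

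**Conclusion.** The definition is wrong as written. Followed literally, it yields tumour status at the end of treatment among those who reach it, not disease-free survival at 12 months from enrolment. It cannot produce the 1, 2 and 5-year results promised elsewhere. Values are missing informatively for patients who die or leave the pathway, contrary to the statement that all patients contribute.

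The contradiction in timing and the lack of a value for these patients rest on the text alone. The effect on the reported percentage depends on assumed rates: 6 points at 10% non-completion and 12 points at 20%, when 60% of completers are clear and non-completers are either left out or counted as failures. Whether the comparison between sequences is biased, by how much and in whose favour, cannot be determined from the documents. The sample size is unaffected.

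**What to change.** Define the endpoint as alive and without evidence of disease at 12 months from enrolment, for every enrolled patient, and apply the same rule at 2 and 5 years.

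- Use the available follow-up imaging nearest the time point, within a stated window. Keep the existing combined radiological, endoscopic and clinical criterion for watch-and-wait patients.
- Count death, recurrence, progression and residual disease as failures.
- Report patients who never enter a surgical sequence as their own group, since the Analysis plan groups by sequence received.
- Report the completion CT as a separate outcome, labelled disease-free at completion of treatment, with the number not completing shown for each group.
- Bring the progression section into line with the same time points, or say that it belongs to the completion outcome.

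A 12-month reading fits the planned follow-up: Data sources and measurements promises at least 12 months of outcome data for the whole cohort at the end of year 3. Later readings depend on the extension, which needs separate funding. On a literal reading, that extension runs to 5 years from study commencement, which gives the last recruits 60 − 24 = 36 months, so the number of patients actually followed to each time point should be stated.

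The cost is a change of definition and of the case report form. The disease-free figure may be lower. A patient still under treatment with residual disease at 12 months will count as a failure at that time, which is a reason to show the completion outcome beside it. The article describes no routine CT near month 12, so where none falls in the window, status must come from the nearest available imaging and the clinical record.
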